**Objective:**

The study aims to determine the effectiveness and feasibility of a proposed 16-week digital intervention program for T2DM self-management and to guide the rollout of a mobile app as part of a population health solution for adults with T2DM in Brunei. The primary outcome of this study is to measure the proportion of participants with a hemoglobin A_1c_ (HbA_1c_) reduction of at least 0.6% from baseline, and the secondary outcomes include a change in HbA_1c_, BMI, lipid profile, and EQ-5D-5L score.

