### Aims and Objectives of Study

The study is conducted with the following aims: to assess the potential effectiveness and feasibility of a comprehensive digital intervention for people with T2DM, to explore the effects of a combined online and offline intervention for the management of T2DM, to improve the accessibility of a lifestyle intervention among participants with T2DM, and to understand the process of guiding the rollout of an app for T2DM management as part of a health management digital solution [19].

The primary objective is to investigate the proportion of participants with a decrease in HbA_1c_ of 0.6% through lifestyle modifications using a digital intervention after 16 weeks. Secondary objectives include estimating the change in HbA_1c_ and BMI, improvement in lipid profile components at week 16, and change in QOL measured by the EQ-5D-5L compared with baseline measurements.

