#### Exclusion Criteria

Individuals will be removed if they meet any of the following exclusion criteria: pregnant/breastfeeding; on insulin therapy or noninsulin injectable medication; a history of diabetes crisis (hypo- or hyperglycemia) in the past 6 months; blood pressure ≥160/100 mmHg; recurrent history of acute pancreatitis; decompensated liver cirrhosis; estimated glomerular filtration rate <60 ml/min/1.73 m^2^; a history of acute myocardial infarction or acute coronary syndrome (within the past 1 year), arrhythmias, or heart failure (New York Heart Association class II-IV); proliferative diabetic retinopathy; foot ulcer or gangrene; deep vein thrombosis of lower limbs (within the past 12 months); intermittent claudication; a history of cerebral hemorrhage or acute cerebral infarction (within the past 12 months); a history of active cancer; posttransplant/perioperative individuals (defined as planned for operation in the next 6 months); a history of hypo- or hyperthyroidism, including subclinical states; musculoskeletal injuries resulting in difficulty in performing physical activities; failure to provide consent; unable to perform activities of daily living; and unable to use WhatsApp and YouTube via mobile devices (eg, phone or tablet).

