### Outcome Measures

#### Primary Outcome

The primary outcome will be the proportion of participants with a decrease in HbA_1c_ by 0.6% through lifestyle modifications via digital intervention after 16 weeks.

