#### Consultations With Clinical Investigators

Consultations with clinical investigators will only be done via the virtual clinics (refer to Figures 3 and 4) that are specifically set up for this study period. Participants with recurrent hypoglycemia and hyperglycemia despite lifestyle modification will be excluded from the study for the participant’s safety. The clinical investigators will write a letter to inform the participant’s primary physician for an urgent review of their treatment. However, participants who do not experience any of the above issues will continue their routine clinic visits (if any) with their primary physician during the study period, and any changes in medications will be noted. Such changes in medication are allowed as part of participants’ usual care and do not constitute an exclusion from the study.

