There are several limitations to this study. The first is achieving the targeted sample size. This will make the evaluation of the primary objective difficult. There is a sample of convenience, which may result in response bias. The nature of a single-arm study will be limited by its nonrandomized design of unknown causal inference. Finally, in the absence of comparison, the reference end point of a 0.6 reduction in HbA_1c_ over 16 weeks was used as a benchmark for clinical effectiveness. Our rationales include the effect of other mobile health interventions on the reduction of HbA_1c_ levels are between a WMD of 0.40 to a mean average of 0.9 [15,16] and the effect of oral diabetic medication as monotherapy is expected to reduce HbA_1c_ by 0.5 to 2.0 [33]. Thus, a lower average number of 0.6 was used. In addition, the absolute and relative decrease in HbA_1c_ will be calculated as secondary outcomes.

This study is expected to conclude in April 2023. The scientific findings will be presented as oral communications and abstracts at regional, national, and international scientific meetings related to T2DM. The findings will also be published in peer-reviewed journals.

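### The primary outcome credits the HbA1c fall to lifestyle change, but drug changes are permitted and those participants are kept in a single-arm trial, so the proportion cannot be read as a lifestyle effect

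*Protocol article*

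**What the plan says.** The article states the primary outcome in two ways.

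- **With attribution to lifestyle.** Outcome Measures, Primary Outcome, counts participants whose HbA1c falls "by 0.6% through lifestyle modifications via digital intervention after 16 weeks". Aims and Objectives of Study has the same idea: a decrease "of 0.6% through lifestyle modifications using a digital intervention after 16 weeks".
- **Without attribution.** The Objective in the Abstract asks only for a "reduction of at least 0.6% from baseline", whatever the cause.

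Consultations With Clinical Investigators deals with medication. Participants without recurrent glycaemic problems continue routine visits to their own physician, and "any changes in medications will be noted. Such changes in medication are allowed as part of" their usual care. The section adds that a change is no ground for exclusion. Participants with recurrent hypo- and hyperglycaemia despite lifestyle modification are removed from the study.

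Three other places bear on the point:

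- Study Design describes a single-arm, nonrandomized trial.
- The Discussion (Overview), in justifying the 0.6 benchmark, says that "the effect of oral diabetic medication as monotherapy is expected to reduce HbA_1c_ by 0.5 to 2.0".
- Sample Size Calculation tests a null proportion of 0.5 against 0.63, with 120 evaluable participants and a one-sided exact test at 0.025.

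**The concern.** An endpoint worded as a fall through lifestyle change, counted in people whose drugs may be started or increased during the same 16 weeks, mixes two causes. Entry requires HbA1c of at least 7%, so intensification in routine care is plausible. Without a control arm, nothing in the design separates the drug effect from the programme effect. By the article's own figure, a drug change can be large enough to make someone a responder.

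The exclusion of people "on insulin therapy or noninsulin injectable medication" applies at entry. The text does not say how someone who starts such a treatment later is classified.

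The interpretation of the headline result is at stake. The trial has a formal hypothesis and a power calculation, and its evidence is meant to guide a nationwide rollout. A proportion reported under the lifestyle wording would be taken as showing what the programme's lifestyle component achieves, and the retention rule does not allow that reading.

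**Working it through.** **1. The texts side by side.** The Primary Outcome and Aims sections require a fall caused by lifestyle. Consultations With Clinical Investigators keeps participants whose medication changes. The endpoint is a proportion of participants, and the article gives no separate class for those with a change. The retention rule fits the Abstract's definition, but not the wording of the Primary Outcome and Aims sections.

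**2. Drug effect against the threshold.** The stated range for oral monotherapy is 0.5 to 2.0. The part at or above 0.6 is (2.0 − 0.6)/(2.0 − 0.5) = 1.4/1.5, or 93% of its width. This is a share of a range, not a probability of response. It shows only that a single drug can reach the threshold and need not.

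**3. The plan's own figure.** Inputs from Sample Size Calculation: n = 120, p0 = 0.5, p1 = 0.63, one-sided exact test at 0.025.

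- Smallest r with P(X ≥ r | 120, 0.5) ≤ 0.025: r = 71 gives 0.0274, r = 72 gives 0.0177. The cut-off is 72 of 120 and the attained level is 1.8%.
- Power: P(X ≥ 72 | 120, 0.63) = 0.782, against the stated 80%. This is close enough for the present purpose.

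**4. Illustration of the bias.** The article gives no rate of medication change and no response rate after one, so both are assumed. Let m be the share intensified, q their response rate, and 0.50 the response without intensification.

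Observed proportion: p = 0.50(1 − m) + q·m. Chance of passing: P(X ≥ 72 | 120, p).

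| m | q | p | Chance of passing |
|---|---|---|---|
| 0 | – | 0.500 | 1.8% |
| 5% | 0.80 | 0.515 | 3.8% |
| 10% | 0.80 | 0.530 | 7.4% |
| 20% | 0.80 | 0.560 | 21.5% |
| 20% | 0.70 | 0.540 | 11.0% |
| 20% | 0.90 | 0.580 | 36.4% |

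Only intensification is modelled. Reductions in medication would lower p.

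**5. Cost of a composite primary outcome.** Suppose 0.63 includes participants with a start or increase, that they respond at the same rate (q = 0.63), and that they are recounted as non-responders. Then p = 0.63 − 0.63·m, with the null held at 0.5 and the cut-off at 72:

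- m = 5%: p = 0.63 − 0.0315 = 0.5985, power 53%.
- m = 10%: p = 0.63 − 0.063 = 0.567, power 26%.

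The starting power was 78%.

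**The case against.** The case on the other side is substantial.

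- **Keeping everyone is a legitimate estimand.** Following all participants under the programme plus usual care is a treatment-policy strategy, and the Abstract's definition agrees with it. This stands. The fault lies in the lifestyle wording, not in retaining these participants.
- **The limitation is partly disclosed.** The Discussion concedes that a nonrandomized single arm limits causal inference. This also stands, but it does not mention medication changes, and the endpoint wording still asserts a cause.
- **An analysis plan may deal with it.** A reader might infer that the changes are recorded and never used. The article does not support that: it says that "any changes in medications will be noted" and is silent on their use, and a full protocol or analysis plan may specify it. The conflict between the endpoint wording and the retention rule is nevertheless in the text shown.
- **The false-success figures depend on what the null means.** A reader might take them as an estimate of the trial's error rate. They are not. The article never says that the 0.5 null excludes usual-care prescribing. If it includes it, the figures do not measure an inflated error rate. At low rates the effect is also small: 3.8% at 5% intensified.
- **One drug is not always enough.** The range starts at 0.5, below the threshold, and is for monotherapy, whereas some recruits already collect oral diabetic medication. The removal of participants with recurrent hypo- and hyperglycaemia may also take out some of those most likely to be intensified.

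These points limit the claimed size and shape the remedy. They do not reconcile the wording.

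**Conclusion.** The point holds as a conflict in stated text. The outcome is defined by a cause that neither the retention rule nor the single-arm design can isolate, so the primary proportion as written cannot be read as a lifestyle effect.

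The size of the bias cannot be determined from the article. Under the assumed 50% and 80% response rates, the chance of passing rises from 1.8% to between 3.8% and 21.5% for 5% to 20% intensified. This rests on assumed rates, on reading the 0.5 null as response without intensification, and on ignoring reductions in medication. The stated sample size is not affected unless the endpoint is redefined.

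A stronger conclusion, that the trial will count a substantial number of drug responders as programme successes, would need a rate of medication change that the article does not give.

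**What to change.** 1. In Aims and Objectives of Study and in Primary Outcome, remove the clause attributing the fall to lifestyle. Use the Abstract's definition: a reduction of at least 0.6% from baseline at week 16, under the programme plus usual care, regardless of medication change. Do not attribute the result to lifestyle alone in reporting.
2. Prespecify a sensitivity analysis that counts as a non-responder anyone with a start or increase of a glucose-lowering drug between the baseline and endline samples.
3. Report how many participants had increases and how many had decreases.

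These steps change wording and analysis only. They use information the article says is already noted, leave the sample size and power as stated, and alter no clinical rule. At the reported status (72 recruited, 12 with endline assessment by 4 November 2022) they could be set before the final analysis, with the change dated and documented.

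If the sponsor prefers the composite in step 2 as the primary outcome, the cost is larger. The null proportion, the target proportion and the power in Sample Size Calculation must all be restated for that endpoint, since power could fall to 53% or 26% under the assumptions shown in the working. It would also count as failures some people who reached the threshold through lifestyle change despite a drug change.

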**Figure 3 figure3:**
[figure not shown]
Video consultation appointment arranged via BruHealth app.

**Figure 4 figure4:**
[figure not shown]
Video consultation interphase via the national health care app (BruHealth).

### Ethics Approval

This study is being conducted in accordance with Good Clinical Practice, as defined by The International Council for Harmonisation. The trial protocol has received approval from MHREC from the Ministry of Health Brunei (MHREC/MOH/2022/4(1)). The appropriate participant information sheet and informed consent form describing in detail the trial interventions, trial procedures, and risks were approved by the ethical committees. Aside from providing a participant information sheet to all potential participants, the investigator will explain the study and answer any questions posed. After being given adequate time to consider the information, the participant will be asked to sign the informed consent document. The participant may withdraw from the trial at any time by withdrawing their informed consent. The rights and welfare of the participants will be protected by emphasizing to them that the quality of medical care will not be adversely affected if they decline participation.

## Results

The enrollment period of this study is between April 18 and November 30, 2022. As of November 4, 2022, a total of 72 participants have been recruited. In this study, participants are recruited in batches, and at the data collection level, there are 12 participants who have completed the endline assessment. Data collection is ongoing. We anticipate this study to conclude by April 2023, followed by data analysis and final reporting with the intention to publish.

## Discussion

### Overview

This study protocol provides an overview of the methodology used in the DEsireD clinical trial. To our knowledge, this study is the first to examine the effectiveness of a proposed 16-week digital intervention program for T2DM self-management and to explore the feasibility of the proposed model of care—a combination of online and offline management to improve the accessibility of a lifestyle intervention among individuals with T2DM in Brunei.

With resource limitations in providing holistic lifestyle interventions in a conventional manner through face-to-face consultations in outpatient settings, digital interventions can be a scalable and cost-effective solution for diabetes self-management. According to Koh et al [19], COVID-19 has had a negative impact on noncommunicable diseases (NCDs) in Brunei due to the disruption of essential health services. Thus, the government has stated its intention to use BruHealth to prioritize NCD service expansions. This includes a diabetes digital intervention. Globally, there are multiple studies demonstrating the effectiveness of digital interventions [12-17,28,29], but there are limited studies conducted in Southeast Asia, particularly in Muslim-dominant populations [16]. This study will be useful for health care professionals and policy makers to understand the possible barriers to the implementation process during the subsequent phases of rolling out an app for T2DM management as a nationwide digital health solution in Brunei [19]. In addition, a feedback form will be given to any participants who have dropped out or completed the study to collect their quantitative feedback on the DEsireD trial. This will include overall experience, the usefulness of the designed program to assist them with setting goals, study duration (16 weeks), and qualitative feedback on the overall perception and contextual feasibility.

The majority of studies use the reduction of the HbA_1c_ level as a clinical marker for the effectiveness of digital interventions for patients with T2DM [16,30]. We agree with Stevens et al [16] that a wider measure of clinical effectiveness should go beyond HbA_1c_. Thus, this study will investigate changes in fasting blood glucose, lipid profile, and health-related QOL (measured by the assessment of the EQ-5D-5L [31,32]).

There are several limitations to this study. The first is achieving the targeted sample size. This will make the evaluation of the primary objective difficult. There is a sample of convenience, which may result in response bias. The nature of a single-arm study will be limited by its nonrandomized design of unknown causal inference. Finally, in the absence of comparison, the reference end point of a 0.6 reduction in HbA_1c_ over 16 weeks was used as a benchmark for clinical effectiveness. Our rationales include the effect of other mobile health interventions on the reduction of HbA_1c_ levels are between a WMD of 0.40 to a mean average of 0.9 [15,16] and the effect of oral diabetic medication as monotherapy is expected to reduce HbA_1c_ by 0.5 to 2.0 [33]. Thus, a lower average number of 0.6 was used. In addition, the absolute and relative decrease in HbA_1c_ will be calculated as secondary outcomes.

This study is expected to conclude in April 2023. The scientific findings will be presented as oral communications and abstracts at regional, national, and international scientific meetings related to T2DM. The findings will also be published in peer-reviewed journals.

### Conclusions

The DEsireD study will be the first study to investigate the clinical effectiveness of the proposed 16-week digital intervention program tailored for individuals with T2DM in Brunei.

The evidence will serve as a guide to roll out a nationwide value-based care program via an app as a digital solution. The lessons from the implementation of this study and the feedback and data from participants will be beneficial for further localization of this digital intervention program. Consequently, scaling up to other NCDs and validation with a larger sample size to demonstrate that the digital intervention is a safe, scalable, sustainable, and cost-effective approach in Brunei will be needed.

This research received no specific grant from any funding agency in the public, commercial, or not-for-profit sectors.

## Abbreviations

Bru-HIMS: Brunei Darussalam Healthcare Information and Management System
DEsireD: Development and Exploration of the Effectiveness and Feasibility of a Digital Intervention for Type 2 Diabetes Mellitus
DiRECT: Diabetes Remission Clinical Trial
HbA_1c_: hemoglobin A_1c_
IDF: International Diabetes Federation
MHREC: Medical and Health Research & Ethics Committee
NCD: noncommunicable disease
QOL: quality of life
RIPAS: Raja Isteri Pengiran Anak Saleh
T2DM: type 2 diabetes mellitus
WMD: weighted mean difference
